## Abstract

**Background:**

Across the United Kingdom (UK), there are increasing calls for the implementation of multi-agency approaches to addressing violence or criminal exploitation outside the home (i.e. extra-familial harm) that address the needs of the child/young person (and their families) and the neighbourhood context in which harms occur. However, to date, there is very little evidence on what an effective multi-agency approach to supporting children and young people, and their families, looks like, or the services they should provide. This article presents the protocol for a feasibility and pilot study of a specialist multi-agency team embedded in neighbourhoods to support children and young people, and their families, who are at risk of, or experiencing, violence or criminal exploitation outside the home.

**Methods:**

A mixed-methods feasibility and pilot study will examine implementation across five UK sites. Pre- and post-outcome measures will be collected from ~1000 children/young people receiving targeted support (~200 per site). Interviews will be undertaken with children and young people, parents/carers, and stakeholders to examine views and experiences of programme implementation and outcomes/impacts, and as relevant evaluation design and outcome measurements. The extent to which findings from the feasibility and pilot study support progression to a full impact study will be reviewed. If a randomised controlled trial (RCT) is not feasible, we will explore a quasi-experimental (natural experiment) evaluation design, using the ‘Target Trial Framework’ to make explicit where a future evaluation will align with, and where it deviates, from the ideal target trial (RCT).

**Discussion:**

This study will provide an important and timely contribution to the emerging, but limited, evidence base surrounding the implementation of place-based multi-agency interventions to support children, young people, and their families at risk of extra-familial harm. This work has direct implications for informing UK policy and practice in the wake of the Independent Review of Children’s Social Care (2022), which called for a ‘whole system reset’ including an improved, multi-disciplinary ‘revolution in Family Help’ to improve outcomes for children and young people, and their families.

**Protocol registration:**

The full study plan is available here: https://youthendowmentfund.org.uk/wp-content/uploads/2024/07/REVIEWED-YEF-AC2-Feasibility-Pilot-Study-Plan-FINAL-July-2024.pdf and via the Open Science Framework: https://osf.io/s9bux/.

**Supplementary Information:**

The online version contains supplementary material available at 10.1186/s40814-025-01736-z.

## Background

Experience of violence or criminal exploitation outside the home (also known as extra-familial harm) can include child sexual and/or criminal exploitation; peer sexual abuse; child radicalisation; teenage abuse in intimate relationships; and serious violence in public places [1–8]. These harms can emerge in children and young people’s peer groups, public and school settings [2, 3], with adults outside of the family unit, within the wider community and/or online [8–11]. The impact of these harms on children and young people is wide-ranging and includes poor mental health, threats to physical health (including potentially fatal violence), criminalisation, and negative impacts on future outcomes and achievements [11]. Importantly, young people who have been coerced to carry out criminal activities can be treated as perpetrators rather than as victims. This can lead to potentially lifelong impacts, with this blurred victim/perpetrator role not easily responded to by services who may be better suited to working with either one or the other [8, 12, 13]. Furthermore, families may be impacted due to threats of violence and death to silence and control the victim or being forced to settle debts. This also results in victims being unable to speak openly to professionals who may be able to help [8].

Evidence suggests that children and young people at risk for extra-familial harm often reach ‘critical moments’ in their lives (such as being excluded from school, physically injured, or arrested), when a ‘decisive response’ is paramount in making a difference to their long-term outcomes [14]. In the United Kingdom (UK), there has been an increased focus amongst child protective services, policymakers, and researchers on extra-familial harms and how this can be supported by child protective systems, including a shift in UK welfare policy to include place-based approaches. This has led to the formation of local safeguarding partnerships between stakeholders such as crime reduction agencies and welfare systems [11]. Further, contextual safeguarding is a framework implemented across local authorities in England and Wales to necessitate that child protective systems: target the social conditions of abuse; incorporate extra-familial contexts in child protection legislative frameworks; use partnerships with individuals and organisations responsible for the spaces where young people spend their time; and measure contextual outcomes [15].

Recent research shows that multi-agency partnerships and child welfare agencies often do not prioritise the social conditions of abuse, but rather target individual behaviour [11]. This omission can negatively impact children and young people as it does not adequately address the contextual factors that increase risks of extra-familial harm. Firmin [12] suggests that the barriers to dealing with extra-familial harms are the policy and practice frameworks they are grounded in, not the legislation that deals with harms outside the home. For example, traditional practices amongst child protective and welfare services do not have a category of ‘extra-familial harms’ within their frameworks, resulting in them using tools that are designed for abuse or neglect.

The UK Government’s Independent Review of Children’s Social Care highlighted that the ‘*current children’s social care system was increasingly skewed to crisis intervention, with outcomes for children that continue to be unacceptably poor and costs that continue to rise*’, and that ‘*for these reasons, a radical reset is now unavoidable*’ [16]. Amongst its recommendations, the report called for changes to the children’s social care response so that children, young people, and families receive more responsive, respectful, and effective support. This included recommending the introduction of one multi-disciplinary Family Help Team that covers both early targeted help and child in need, to reduce referral and handovers between services/teams, and ensure the provision of meaningful support. Teams would be based in community settings that are known to and trusted by families (e.g. schools, family hubs), and composed of multi-agency professionals including family support workers, domestic abuse workers, mental health practitioners, and social workers. Critically, the service offered to children and young people, and families would be tailored to their needs, and that of the neighbourhood, identified via robust needs assessment and feedback from families.

However, to date, there is very little evidence on what an effective multi-agency approach to supporting children and young people, and families looks like, or the services they should provide, particularly in the context of extra-familial harm [17]. Given the emerging but limited evidence on such programmes, we present the protocol for a feasibility and pilot study of a specialist multi-agency team embedded in neighbourhoods to support children and young people, and their families, who are at risk of, or experiencing, violence or criminal exploitation outside the home (the Youth Endowment Fund [YEF] Agency Collaboration Fund: Supportive Home Programme [herein ACF2]; [18]). This study will explore dimensions of, and factors affecting implementation, early signs of change and change mechanisms, and the feasibility and options for progression to an impact study.

### Aims and research questions

This mixed-methods study will be implemented in two concurrent and complementary phases which aim to (i) assess the feasibility of programme implementation and (ii) assess the feasibility of, and pilot an impact evaluation, and present an options analysis/recommendation for an impact study. Research questions for each phase are presented in Table 1.

**Table 1 Tab1:** Research questions

Feasibility of implementation	1a. Can the programme be implemented with fidelity to the programme/site-level theory of change and delivery framework? 1b. Does the programme implementation plan and/or theory of change need refining? 1c. What is the programme recruitment, retention, and reach across strands? 1d. Is there a clear and consistent set of eligibility criteria being adhered to across and activity strands, that also reaches keyworker pathway pilot targets? 1e. What does programme referral, engagement, support offer, and completion look like for children and young people (and their family/carers) through the key worker offer and other programme activities? 1f. What factors support or impede programme delivery (including consideration of intervention characteristics, referral pathways and information sharing; delivery and multi-agency partner capacity experience, partnership working, skills and attitudes; workforce composition; implementation support systems; and community/system level factors)? 1g. What are service users and practitioner’s views and experiences of the programme?
Feasibility of and pilot of an impact evaluation	2a. What is the level of consistency and standardisation of programme implementation across the five sites overall? 2b. Are sites aligned enough in their aims and approaches to make a collective impact study feasible? 2c. What is the feasibility of measuring impact at an individual, site, and programme level? 2d. What is the required sample size for a full impact evaluation? 2e. Is it feasible to achieve a sample size with enough power to progress to an impact study? 2f. Across sites, is the programme sufficiently distinct from business as usual for an impact evaluation to be feasible? 2g. What is the direction and magnitude of potential changes in identified outcomes, and does the programme achieve its intended outcomes? 2h. Are the piloted outcomes/measures appropriate/practical/reliable/valid for the programme? 2i. What are the options and considerations for design of an impact study (e.g. What potential is there for randomisation at individual or area level; do any sub-group effects need to be considered and why)? 2j. What scale of delivery would be required for the sample size to be met, given the evaluation design being recommended at the end of the feasibility study (e.g. how many sites, how many neighbourhoods in each site)? 2k. What research questions could a robust impact evaluation answer? 2l. What is the acceptability of an impact evaluation to programme stakeholders? 2m. Do sites have the capacity to scale up if the study progresses to a full impact evaluation (considering pilot recruitment/retention/reach and local needs/systems)?

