### Sampling, participant recruitment, and eligibility criteria

#### Sample size

For the feasibility and pilot of the impact evaluation phase of this study, pre- and post-outcome measures will be collected from 1000 young people who receive key worker support (~200 per site). This sample size target was a pragmatic decision, agreed a priori between the evaluation team and the funder (YEF), on the basis that this would provide a good indication of intervention reach and of the ability of sites to recruit a sufficient number of participants to evaluate impact in a full trial. Our target number of 10 neighbourhoods exceeds the 8 identified by Hemming and colleagues in their overview of external pilot studies [20], and our total sample size exceeds the 30 participants per site recommended by Lancaster et al. [21] and the 35 per group recommended by Teare et al. for estimating the uncertain critical parameters (including standard deviation for continuous outcomes, and consent, event, and attrition rates for categorical outcomes) [22]. For the feasibility of the implementation phase of this study, interviews will be completed with 100–125 stakeholders (20–25 per site), 75 children and young people (15 per site), and 75 parents/carers (15 per site). Participants will be selected purposefully to ensure diversity across and within sites. For stakeholders, the number of participants will be guided by the delivery context of each multi-agency team and saturation. Children and young people and parents/carers will be purposefully sampled (in collaboration with gatekeepers who provide a safeguarding role) to ensure diversity in relation to socio-demographics and guided by saturation.

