#### Assessment of primary and secondary data

As this is a feasibility and pilot study, no inferential analyses will be undertaken. Descriptive analyses of all key outcomes will be conducted to provide an overview of data, to describe the target group and properties of aggregate datasets.

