**Additional criteria**				
** (Adverse) effects of programme participation**	From preliminary analysis of outcome data and qualitative data	No evidence of substantial negative effects of participation		Evidence of substantial negative effects of participation
** Acceptability of programme activities**	From analysis of qualitative data	Target groups report programme activities and interventions are acceptable and/or could be feasibly improved	Target groups report programme activities/interventions are unacceptable and cannot identify how they could be improved. Sites develop plan to increase acceptability	Target groups report programme activities/interventions are unacceptable and cannot identify how they could be improved. Sites cannot identify a plan to increase acceptability
** Acceptability of evaluation methods**	From analysis of qualitative data	Target groups report evaluation methods are acceptable and/or could be feasibly improved	Target groups report evaluation methods are unacceptable and cannot identify how they could be improved. Evaluator/sites develop a plan to increase acceptability	Target groups report evaluation methods are unacceptable and cannot identify how they could be improved. Evaluator/sites cannot identify a plan to increase acceptability
** Programme implementation**	From analysis of theories of change and system maps, and interviews with providers	Programme is coherent: meets criteria for multi-agency approach and is distinct from business as usual	Programme is not coherent: does not meet criteria for multi-agency approach and is not distinct from business as usual. Sites identify plan to improve coherence	Programme is not coherent: does not meet criteria for multi-agency approach and is not distinct from business as usual. Sites cannot develop a plan to improve coherence

^a^RIP—Research in Practice, the programme co-design partner

^b^E.g. weekly

^c^E.g. 6-monthly, annually

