The study has some limitations. Ideally follow-up data would be collected at +6 months, as behavioural change and changes to wider family/contextual factors are expected to take time. Further, despite the inclusion of areas with high levels of youth violence and/or exploitation, the incidence of engagement in violence or criminal exploitation during this time period may be low. This may lead to difficulties in detecting any early markers of change. However, due to the piloting period being 11 months, and the uncertainty of when and how well recruitment will proceed, and if so, how long children and young people will stay engaged in the programme, for the pilot period we are implementing a +3-month follow-up period to ensure that baseline and follow-up data are collected. This will mean that the follow-up data collection period may not mimic a future impact study design. We also note that while our criteria for progression to a full impact evaluation study apply to both treatment and control groups, for pragmatic reasons data collection and outcome scoping have been limited to participating sites (treatment groups) within this feasibility and pilot study. Considerations around the availability and suitability of outcome data for control sites will be considered as part of control site selection if this study proceeds to full impact evaluation.

A key output from this study will be a feasibility and pilot study report. This will include an updated programme-level theory of change and clearly defined programme implementation model(s); key lessons from programme implementation and recommendations for refinement; and an assessment of the feasibility of progressing to an impact study including considerations and options for progression to an impact study using the Target Trial Framework [31]. This will not only build on the limited evidence base for these types of programmes, but also support the development of robust approaches for evaluating complex place-based approaches for preventing violence amongst children and young people [34]. Involving the community in place-based evaluations is critical [30]. For this study, children and young people have informed study design and implementation (i.e. review of research tools and approaches) and will be key to developing a child-friendly summary of the feasibility and pilot study, ensuring findings are disseminated to those the programme aims to support.

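### The second clause of research question 2g asks whether the programme works, which before-and-after data from treated sites alone cannot show; absence of observed worsening is likewise not evidence of no harm

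*Protocol article*

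**What the plan says.** Table 1 of the protocol article (Aims and research questions) puts question 2g as: "What is the direction and magnitude of potential changes in identified outcomes, and does the programme achieve its intended outcomes".

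Under Data collection and outcomes, young people complete questionnaires when they engage with a key worker and again 12 weeks later. The Discussion states that "data collection and outcome scoping have been limited to participating sites (treatment groups) within this feasibility and pilot study". Under Assessment of primary and secondary data, the analysis is limited as follows: "As this is a feasibility and pilot study, no inferential analyses will be undertaken". The next sentence adds: "Descriptive analyses of all key outcomes will be conducted to provide an overview of data".

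In Table 3, follow-up questionnaire completion of 60–100% is fully met and 40–59% partially met. The row on adverse effects of participation is fully met by "No evidence of substantial negative effects of participation". Its stated source is "From preliminary analysis of outcome data and qualitative data". That row has no middle level, and the article does not say what makes an effect substantial.

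**The concern.** Whether a programme achieves its intended outcomes is a causal question. It asks whether outcomes differ from what they would have been without the programme. A before-and-after description of one treated group does not supply that contrast.

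Two ordinary mechanisms could move the observed change with no programme effect. First, young people may enter at a bad time: the Background refers to critical moments "such as being excluded from school, physically injured, or arrested". Scores taken at such a time may drift back towards the person's usual level. Second, those who return a second questionnaire may differ from those who do not.

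The negative-effects row has the same weakness. It asks about effects of participation, but nothing in the study shows what would have happened without participation. If average scores do not worsen, that may reflect no harm, or harm offset by natural recovery or by loss of those who did badly.

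At stake is a pilot report that answers 2g as written and so gives an effectiveness conclusion the data do not support, or that treats a lack of observed worsening as reassurance.

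**Working it through.** **The plan's own figure.** Five sites at about 200 each: 5 × 200 = 1000, which agrees with the stated target. The Sample size section calls the target pragmatic, so there is no power calculation to reproduce.

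**Inputs.** From the article: 1000 young people, 60% as the lower limit of fully met for both baseline and follow-up completion, and no comparator. Assumed, because the article gives no values: pre-post correlation r = 0.5 to 0.8, entry distance d = 0.5 to 1.0 SD worse than the long-run mean, equal SD at both times, and no clustering.

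**Step 1: is precision the obstacle?** In baseline-SD units the SD of change is √(2(1 − r)), so the 95% half-width is 1.96 × √(2(1 − r)) / √n. The denominator of the follow-up row is not spelled out, so two readings are shown.

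| Pairs | r = 0.5 | r = 0.8 |
|---|---|---|
| 600 (60% of 1000) | 0.080 | 0.051 |
| 360 (60% of 60% of 1000) | 0.103 | 0.065 |

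Overall mean change would be estimated to within about 0.05 to 0.10 SD. With an assumed design effect of 1.5 the widest of these becomes 0.127. Sample size is not the main problem.

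**Step 2: regression to the mean.** Expected apparent improvement with no effect is (1 − r) × d.

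- d = 0.5, r = 0.8: 0.2 × 0.5 = 0.10 SD
- d = 0.5, r = 0.5: 0.5 × 0.5 = 0.25 SD
- d = 1.0, r = 0.8: 0.2 × 1.0 = 0.20 SD
- d = 1.0, r = 0.5: 0.5 × 1.0 = 0.50 SD

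The range is 0.10 to 0.50 SD.

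**Step 3: selective follow-up.** Suppose a share p is followed up and shows mean change c. The mean change over everyone is zero if the rest change by −c × p / (1 − p). With p = 0.60 and an illustrative c = +0.20 SD, this is −0.20 × 0.60 / 0.40 = −0.30 SD. A follow-up rate scored as fully met therefore leaves room for the overall change to be nil.

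**Step 4: what follows.** Under these assumptions the possible bias is as large as, or larger than, the half-width of the interval. An interval describes sampling variation only and does not remove the bias.

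**The case against.** The strongest defence is that the article never plans an effectiveness claim. It speaks of early signs of change, bars inferential analysis, and says that a randomised trial would give the strongest evidence of effectiveness. Its limitations mention short follow-up, low incidence and data from treated sites only. Table 3 has no efficacy row, so a spurious improvement cannot trigger progression through 2g. All of this is correct and lowers the severity. None of it limits the second clause of 2g, which stands as a present-tense effectiveness question.

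A reader might go further in four ways that the documents do not support.

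- *That the negative-effects row passes by default.* The row also draws on qualitative data. Interviews are planned with 75 young people, 75 parents or carers and 100–125 stakeholders. The analysis is to capture unintended consequences as interviewees perceive them, and the team aims to interview early leavers sooner. The criteria are to be weighed with the funder, not applied mechanically. What remains is that key workers identify the young people and parents to be interviewed, and that there is no comparison group.
- *That the pre-post change will become the effect size in 2d.* No text says so. The parameters named in the Sample size section are the SD and the consent, event and attrition rates.
- *That bias must run towards improvement by a known amount.* Eligibility has no SDQ threshold, support extends to early help, and critical moments are background, not an entry rule. If need is persistently high, scores need not regress. The direction of follow-up bias is not established either.
- *That intervals are excluded.* The article bars inferential analysis but does not expressly bar descriptive intervals, and the full plan is not shown.

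**Conclusion.** The concern holds for the second clause of 2g. With no comparator and only descriptive analysis, the study can report the direction and size of observed change but not whether the programme caused it. No later analysis plan can supply the missing comparison group.

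For the negative-effects row the conclusion is narrower. Its two data sources can raise harm signals, but without a comparator a lack of average worsening does not show that there is no harm.

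The 0.10 to 0.50 SD range is purely illustrative. It rests on an assumed entry distance and correlation, and on the premise that young people enter at a temporary low point. The restriction to those with both questionnaires is an inference from the arithmetic of change, because the article names no analysis set. Severity: should-fix.

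**What to change.** 1. Delete the second clause of 2g, or reword it as observed change that is not attributable to the programme.
2. Report mean change with the number of pairs and a descriptive 95% CI, and compare baseline SDQ between those with and without follow-up. The interval shows precision and does not cure bias; the comparison shows how selective follow-up may have been.
3. State that the pre-post change will not be used as the effect size in 2d. This is a safeguard, since no such use is planned in the text.
4. Recast the negative-effects row as a review of harm signals from outcome data, interviews and existing monitoring data, including attrition. Say that absence of mean SDQ worsening cannot by itself give a fully met rating.

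Two further steps are not requested. The proportion worsening by a set SDQ amount would still be uncontrolled before-and-after data. Safeguarding outcomes for every starter are not among the monitoring items listed, and could need new data collection after delivery began in April 2024.

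The cost is wording, a few extra descriptive tables and a more modest claim in the report.
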